#### Recruitment

A total of 110 patients (M/F) will be recruited with uncertain diagnosis of cognitive impairment, as consecutively sent for ^18^F-FDG PET-MR imaging in their workup (estimated subgroup size: 50 patients with aMCI-AD; 20 patients with DLB; 20 patients with FTD; 20 patients with late-life psychiatric disorder). A minimal age was set at 30 years old, but the expected age ranges from 50 until +/- 85y old. The neuropsychological testing is expected to already be obtained during the diagnostic assessment. Some additional tests on top of those from the memory/referral clinic may be foreseen if necessary to ensure coverage of all relevant domains. The main sources of referrals constitute the UZ Leuven memory clinic of neurology, psychiatry, a collaboration with geriatrics and external hospitals situated in proximity of Leuven.

For the recruitment of HV, we will make use of (I) advertisements in targeted local journals and on the bulletin boards in the buildings of KU Leuven and UZ Leuven, on the websites of UZ/KU Leuven and in social media, and (II) of the volunteer database of the Center for Clinical Pharmacology. Forty screened HV (M/F) aged 18–85, approximately evenly spread over decades, will be included. These volunteers are screened for general good health condition (based on medical history, physical examination including vital parameters and clinical laboratory test and urinalysis), for neurocognitive and executive functioning via neuropsychological assessment, for amyloid status with amyloid PET scan (^18^F-NAV4694) if > 50y (below amyloid negativity is presumed) and for existence of other possible exclusion criteria.

#### Screening

Study participants will first be subjected to a screening visit during which the study protocol will be explained in detail. Thereafter, the informed consent form will be signed by all participants– or their legal representative in case of patients who are unable to give consent themselves– prior to study inclusion. In HV, a Mini-Mental State Examination (MMSE) will be used to assess global cognition, and depressive symptoms will be screened through the Beck Depression Inventory (BDI). Furthermore, to assure general good health in this group a thorough blood analysis and urinalysis are executed with assessment of hematology, coagulation and chemistry for blood and pH, hematuria, leukocyturia, glucosuria, proteinuria and epithelial cells for urine.

### Data collection and analysis

#### Imaging

All scans will be performed at the Nuclear Medicine PET-MR unit of the University Hospital Leuven, on a General Electric (GE, Milwaukee, WI, USA) Signa PET-MR (time-of-flight (TOF) PET, 3-Tesla MR) scanner. A validated zero echo time (ZTE) sequence will be used for attenuation correction [55]. ZTE allows MR imaging of bone, which enables better skull segmentation, tissue assignment and accurate PET quantification. All tracers will be produced in-house.

##### ^18^F-SynVesT-1 PET-MR

During the first scan visit, the ^18^F-SynVesT-1 PET-MR scan will be acquired as a measure of synaptic density (SV2A). The tracer will be administered through a venous catheter with an intended dose of 150 MBq (± 10%).

For patients, a static 30-minute PET acquisition will be conducted, starting 60 min post injection. For HV, an arterial catheter line will be placed in a radial artery for arterial blood sampling. The scanning protocol consists of a dynamic PET acquisition of 90 min starting at time of injection, with arterial input function via arterial blood samples for full kinetic modelling and investigation of the reference region. Discrete blood samples will be manually collected every 10s from 10 to 90s; every 15s from 90s to 3 min; and then at 3.5, 5, 6.5, 8, 12, 15, 20, 25, 30, 45, 60, 75 and 90 min. Plasma samples for correction of radioactive metabolites will be collected at 3, 8, 15, 30, 60 and 90 min after injection.

For all participants, data will be obtained in list mode and will be reconstructed using an ordered subset expectation maximization (OSEM) algorithm (4 iterations and 28 subsets), with corrections for scatter, random coincidences, deadtime, radioactive decay, and ZTE-based attenuation as described above and with post-filtering with a 3D isotropic gaussian of 4 mm Full Width at Half Maximum (FWHM). ^18^F-SynVesT-1 PET acquisitions for HV will be rebinned into 30 frames (6 × 15 s; 3 × 30 s; 3 × 1 min; 3 × 3 min; 15 × 5 min). ^18^F-SynVesT-1 PET acquisitions for patients will be rebinned into 6 frames of 5 min.

Simultaneously with PET, following MR measures will be acquired from all participants using a vendor-supplied Nova 32 channel coil: structural 3D T1-weighted MR, 3D T2-weighted fluid-attenuated inversion recovery (FLAIR) MR, resting state functional-MRI and triple-plane tagged enhanced ASL perfusion.

##### ^11^C-UCB-J PET-MR

To assess quantitative similarity of ^18^F-SynVesT-1 and ^11^C-UCB-J, both targeting SV2A, 10 HV will additionally receive a dynamic ^11^C-UCB-J PET acquisition 0–90 min post injection using PET-MR, including arterial sampling, following the same acquisition and reconstruction protocol as for ^18^F-SynVesT-1. Again, the tracer will be administered through a venous catheter with an intended dose of 300 MBq (± 10%). No additional MR sequences will be acquired.

##### ^18^F-NAV-4694 PET-MR

^18^F-NAV-4694 PET (formerly known as ^18^F-AZD-4694) has been shown to selectively bind amyloid-β plaques in AD [56] and can accurately determine cerebral amyloid status [57]. Its comparability to the most widely used ^11^C-PiB PET tracer has been demonstrated [58]. For all included HV above 50 years, known cerebral amyloid status is required for inclusion in the study (max 1 year old). If amyloid status is unknown or was not determined recently, a routine 20-minute amyloid PET scan (^18^F-NAV-4694) will be acquired, starting 40 min post injection. This tracer will also be administered through a venous catheter with an intended dose of 120 MBq (± 10%). Data will be obtained in list mode and will be reconstructed using an ordered subset expectation maximization (OSEM) algorithm (2 iterations and 32 subsets), with corrections for scatter, random coincidences, deadtime, radioactive decay, and ZTE-based attenuation as described above and with post-filtering with a 3D isotropic gaussian of 4.5 mm FWHM. No additional MR sequences will be acquired. For practical reasons, ^18^F-NAV-4694 could also be acquired on a PET-CT scanner (TruePoint, Siemens, Erlangen, Germany) and reconstructed using ordered subsets expectation maximization (3 iterations and 21 subsets), with corrections for scatter, random coincidences, deadtime, radioactive decay, and CT-based attenuation, with post-filtering with a 3D isotropic gaussian of 2 mm FWHM.

Amyloid status will be determined by visual interpretation and classified as positive or negative by an expert in nuclear medicine ([name]).

#### Neuropsychological assessment

For HV, the neuropsychological testing for this study consists of a cognitive test battery with subtests of the Cambridge Neuropsychological Test Automated Battery (CANTAB) [59]: motor screening task (MST), reaction time (RT), paired association learning (PAL) and spatial working memory (SWM). To obtain a more complete evaluation of all cognitive domains this also includes the Mini-mental state examination (MMSE) [60] or Montreal Cognitive Assessment (MoCA) [61], Clinical Dementia Rating Scale (CDR) [62], Rey auditory verbal learning test (RAVLT) [63], Boston naming task (BNT) [64], trail making test A and B (TMT) [65], Raven’s colored progressive matrices (RCPM) [66] and animal verbal fluency (AVF) [67]. To screen for depressive, anxious and other important psychiatric symptoms we will use the Symptom Checklist-90 (SCL-90) [68], Beck depression inventory (BDI) [69] and Geriatric depression scale (GDS) [70].

For patients, in case some of the above test domains have not been established, the study team will determine which additional tests of the above on top of the routine neuropsychological testing should be included, if relevant for the suspected disease and also on the base of clinical examination and ^18^F-FDG PET.

#### Data analysis and statistics

All reconstructed ^18^F-SynVesT-1 and ^11^C-UCB-J PET data will be corrected for motion artefacts using PMOD software (v4.1, PMOD Inc. Zurich, Switzerland). The frames of static acquisitions will be averaged and rigidly co-registered to the corresponding T1-weighted MRI. For partial volume correction, a region-based voxel-wise (RBV) correction, which is based on the Yang approach [71–73] will be applied as implemented in an in-house validated pipeline in Python 3.9 [74]. Data analysis will be done using volume-of-interest (VOI) analysis using FreeSurfer 6.0 or python 3.9 for anatomical parcellation and delineation of the VOIs. For voxel-based analysis, PET data will be spatially normalized to template space using a non-linear normalization as obtained by the CAT12 toolbox of statistical parametric mapping (SPM12; Welcome Trust Centre for Neuroimaging, University College London, UK) and smoothed using an isotropic Gaussian kernel with 8 mm FWHM (voxel size: 1.5 × 1.5 × 1.5 mm).

^18^F-SynVesT-1 and ^11^C-UCB-J uptake in HV will be quantified by distribution volume (V_T_) using a one-tissue compartment model as previously validated [26, 52]. For the tracer kinetic modeling of ^18^F-SynVesT-1 in HV, the centrum semiovale will be investigated as a reference region [30, 53] as well as the cerebellum as a pseudo-reference region [42]. For ^18^F-SynVesT-1 patient data, standardized uptake value ratios (SUVR) will be calculated after this reference region exploration in HV.

The evaluation will be done in 3 steps: firstly, referring physicians will be asked to provide suspected diagnoses and confidence scores at predefined moments during clinical workup. Secondly, anonymized scans (orthogonal images, 3D surface rendering and z-score images by comparison to in-house database as clinical routine / comparison to healthy control normal data) with core clinical information will be presented at regular intervals to 3 nuclear medicine physicians with variable experience but after a short reader training in healthy ^18^F-FDG and ^18^F-SynVesT-1 scans. They will provide an image-based diagnosis and indicate the corresponding level of certainty. The different visual readers will then provide a consensus protocol for each scan. After visual reading, also semiquantitative volume of interest- and voxel-based classifications will be carried out (for ^18^F-FDG, ^18^F-SynVesT-1, ASL and rMAPS). Lastly, data will be compared in terms of accuracy based on the consensus clinical diagnosis (about 6 months after ^18^F-FDG scanning). Consensus clinical diagnosis is based on initial clinical findings and evolution, CSF biomarkers (/ amyloid PET), sMRI and ^18^F-FDG PET results. Note that patient data analysis can only be initiated after the finalization of the healthy subject ^18^F-SynVesT-1 database (so z-score images can be obtained).Voxel-based morphology (VBM) and voxel-based cortical thickness (VBCT) analysis, adjusted for total intracranial volume will be used to assess structural gray matter volume and thickness differences in all subjects in the CAT12 toolbox of Statistical Parametric Mapping (SPM12). We will analyze individual imaging modalities (^18^F-SynVesT-1 and ^18^F-FDG PET, ASL, structural MR, rs-fMRI) independently in a univariate analysis to address the different modality, as well as using a multivariate approach as part of the underlying research questions.

Statistical analyses will be performed using GraphPad Prism version 9 (GraphPad Software, La Jolla, CA). Demographic characteristics will be compared between groups using an unpaired Student t-test, unpaired Mann-Whitney U test, Fischer’s exact test or Chi-square test for trend as appropriate. Data normality will be verified by a Shapiro-Wilk test (α = 0.05). Correlation analyses will be performed by a Pearson correlation if data are normally distributed or by a Spearman correlation if data do not follow a normal distribution. Paired student’s t-tests or a non-parametric substitute will be performed in both a voxel-based and a VOI-based analysis to investigate regional differences between ^18^F-SynVesT-1 PET and ASL. Signature patterns of reduced synaptic density for different cognitive disorders will be assessed by comparing ^18^F-SynVesT-1 in patient subgroups versus HV using Student’s t-tests or Mann Whitney U-tests. To explore the diagnostic performance of ^18^F-SynVesT-1 compared to ^18^F-FDG, scans will be visually assessed by different specialists in nuclear medicine/neurologists and diagnostic accuracy (sensitivity, specificity and accuracy) as well as the interobserver agreement will be calculated. All results will be adjusted for multiple comparisons (Bonferroni) and investigated two-sided at a significance level of 0.05.

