**Discussion:**

The main endpoint of the study will be the comparison of the diagnostic accuracy between ^18^F-SynVesT-1 and ^18^F-FDG PET in cognitive disorders with uncertain etiology and in exclusion of a neurodegenerative cause in patients with cognitive impairment in late-life psychiatric disorders. The strength of the relationship between cognition and imaging data will be assessed, as well as the potential incremental diagnostic value of including MR volumetry, ASL perfusion and rs-fMRI.

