Since patients will be included upon referral for ^18^F-FDG PET at the UZ Leuven PET center, the sample will be highly representative for a real-life clinical setting. Another strength of our study is the use of simultaneous PET and MR imaging, which will allow us to investigate multiple modalities with limited associated burden for patients. We believe that achieving the anticipated sample size in an adequate time window is feasible due to this 1-scan study protocol in combination with the considerable extent of the local hospital memory clinic. ^18^F-SynVesT-1 PET will not only provide a cleaner marker of synaptic density, but it also obviates the need (i) for patients to be fasted at least four hours prior to tracer injection, (ii) to delay simultaneous MR scanning to avoid primary auditory cortex activation and (iii) to provide a dark environment prior to scanning to limit visual cortex activation. Furthermore, as visual stimulation has been shown not to change ^11^C-UCB-J levels in the occipital cortex [76], no influence of scanning with eyes open or closed is expected.

As for limitations and compromises made in the design of the study, some sources of bias may be present. Expert visual readers will be more experienced in reading ^18^F-FDG scans compared to ^18^F-SynVesT-1 scans. Therefore, they will be presented a normal dataset for visual inspection before patient reads. Due to clinical need and the importance of ^18^F-FDG PET in the diagnostic work-up, the ^18^F-FDG PET result will likely influence the final clinical diagnosis and might result in a bias in favor of ^18^F-FDG PET. Therefore, anonymized reads will be done also by expert nuclear medicine physicians not involved in the clinical workup.

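### Readers known to be less familiar with SynVesT-1 are trained on healthy scans only, so unfamiliarity with its disease patterns may be counted as tracer inaccuracy

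*Protocol article*

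**What the plan says.** The abstract of the protocol article makes diagnostic accuracy the central question: "The main endpoint of the study will be the comparison of the diagnostic accuracy between" SynVesT-1 and FDG PET. Under Study hypotheses, SynVesT-1 is expected to be non-inferior to FDG in sensitivity and specificity.

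Under Data analysis and statistics, anonymized scans "with core clinical information will be presented at regular intervals to 3 nuclear medicine physicians". The readers are of mixed experience, "but after a short reader training in healthy" FDG and SynVesT-1 scans. Each gives an image-based diagnosis with a level of certainty, and the readers then agree a consensus for each scan. From the visual assessments, "diagnostic accuracy (sensitivity, specificity and accuracy) as well as the interobserver agreement will be calculated". VOI-based and voxel-based classifications follow separately.

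The Discussion lists the experience gap among the possible sources of bias: "Expert visual readers will be more experienced in reading ^18^F-FDG scans compared to ^18^F-SynVesT-1 scans". It then gives the remedy: "Therefore, they will be presented a normal dataset for visual inspection before patient reads".

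**The concern.** The stated remedy does not match the bias that the protocol admits. Normal scans teach a reader to recognize a normal SynVesT-1 image. The scored task is different: to attribute an abnormal image to AD, FTD, DLB or late-life psychiatric disorder. Under the training as described, the first diseased SynVesT-1 scans that it provides for are those of study patients, and those reads already count.

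This is not a detail left to a fuller document. The content of the training is stated in two places, and both name healthy or normal scans only.

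At stake is what the visual comparison measures. Research question (iii) and hypothesis (v) concern the tracer. If readers misattribute SynVesT-1 patterns because they have not seen them before, the estimated difference contains reader familiarity as well as tracer performance, and the familiarity part works against SynVesT-1. The Discussion also admits that FDG contributes to the final clinical diagnosis, which favours FDG too, so the two biases point the same way.

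**Working it through.** The argument rests on setting the sections side by side.

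1. **Task.** Readers give a diagnosis from the image (Data analysis and statistics). The expected groups are 50 aMCI-AD, 20 FTD, 20 DLB and 20 late-life psychiatric disorder (Sample size), 110 patients in all.
2. **Training.** Healthy scans of both tracers, in a short session (Data analysis and statistics), and again a normal dataset (Discussion).
3. **Do FDG reading habits carry over?** The Discussion gives evidence from the related SV2A tracer 11C-UCB-J. In AD, the largest synaptic effects are in the hippocampus and medial temporal regions, whereas FDG shows larger effects in neocortex. In DLB, the FDG deficit was both deeper and wider than the synaptic one. In FTD, the authors knew of no direct comparison with FDG. So for AD and DLB the patterns are reported to differ, and for FTD it is not known whether they do.
4. **Where the error goes.** Sensitivity, specificity, accuracy and agreement are calculated from these reads. A misread from unfamiliarity cannot be distinguished, in those figures, from a scan that is uninformative.
5. **Direction.** The admitted experience gap favours FDG, so the expected bias is against SynVesT-1.

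**Size.** If a share f of the SynVesT-1 reads loses d accuracy points to unfamiliarity, the average loss over the series is f × d. The document gives neither f nor d, so no value follows from it.

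**Can the 10% margin serve as a yardstick?** The sample size section states 8, 10 and 12 per group for true differences of 0%, 1% and 2%, with a 10% margin, alpha 0.025, 80% power and test-retest variability of 5–10%. The usual formula for means is

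n per group = 2 × SD² × (1.960 + 0.842)² / (10 − difference)²

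With an assumed SD of 7, inside the stated 5–10%, the numerator is 2 × 49 × 7.85 = 769:

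- difference 0: 769/100 = 7.7, so 8
- difference 1: 769/81 = 9.5, so 10
- difference 2: 769/64 = 12.02, so 13 (stated 12)

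The noncentral-t version with an assumed SD of 6.5 gives exactly 8, 10 and 12. The stated figures are therefore reproduced as a calculation on a continuous measurement. The margin is on that scale, and the document does not state it as a margin in accuracy points for the visual reads.

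**The case against.** The protocol discloses the gap and offers a partial remedy, so what remains is how far the training should go. The readers also have other help: z-score images against healthy controls show where uptake is abnormal, and three readers reach a consensus. The VOI-based and voxel-based classifications do not depend on visual skill. The Discussion notes that SynVesT-1 data were not yet public, which may explain why no diseased training set is described. Finally, a bias against the new tracer costs power but would not by itself produce a false claim of non-inferiority.

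Much of this stands, and it limits the point. It does not remove it. Z-scores show where uptake is low, but the reader must still link the pattern to a disease. Three readers with the same training can share the same error, and the semiquantitative classifications are separate from the visual figures. The published 11C-UCB-J patterns are available as training content even where SynVesT-1 data are not.

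A reader might infer four stronger claims that the document does not support:

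- **That a failed non-inferiority result could not be told apart from inexperience.** Poor visual reads beside good semiquantitative classification would point towards the readers.
- **That learning affects SynVesT-1 only.** Reader experience is described as variable and the training covers both tracers, so some FDG learning is possible. Only an asymmetry is conceded.
- **That scans are read in order of enrolment and readers improve steadily.** Reading at intervals does not fix the order, patient analysis waits for the healthy database, and no feedback of the final diagnosis to readers is described.
- **That learning would use up a third to three quarters of the margin.** This assumes losses such as 10 points over the first third of reads (10 × 1/3 = 3.3) or 15 over the first half (15 × 1/2 = 7.5), and divides them by a 10% margin tied to test-retest variability. The inputs have no source and the scales do not match.

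**Conclusion.** The point holds in limited form. The protocol admits that readers know FDG better, trains them on healthy scans only, and asks them to assign disease patterns that its own Discussion describes as different between SV2A and FDG imaging in AD and DLB. SynVesT-1 misreads from unfamiliarity, most likely among the early reads, may therefore be counted as tracer inaccuracy in the visual comparison, with a bias against SynVesT-1.

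The direction follows from what the protocol concedes. It assumes that no further disease-pattern training takes place beyond what is stated, and that the 11C-UCB-J patterns carry over to SynVesT-1, as the protocol itself expects. The size is unknown and may be small, given the z-score images, the consensus and the separate classifications. A lower interobserver agreement for SynVesT-1 is possible but not shown. The matter deserves a change because the visual reads feed the main comparison and the change is cheap.

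**What to change.** - **Training.** Before any scored read, extend the session to the published SV2A disease patterns for AD, FTD and DLB, using the 11C-UCB-J results that the Discussion already cites. Use no study patients for this.
- **Reading order.** Randomize scan order within each reading session and record each scan's position. This does not stop learning, but it keeps reading position within a session from being tied to order of enrolment.
- **Reporting.** Give accuracy for both tracers by reading order, beside the semiquantitative classification. A rise for SynVesT-1 but not for FDG would suggest learning. A flat course would not exclude unfamiliarity that lasts throughout, which is why the semiquantitative results belong next to it.
- **Main analysis.** Keep the first reads. A masked re-read of the first block by the same readers is optional and only a sensitivity analysis, since recall of the cases and earlier consensus discussion could influence it.

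The cost is a longer training session and a little more analysis. No additional patients, scans or readers are needed.

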### Study hypotheses

The following specific research questions will be addressed:

(i)Can SV2A PET, using the novel tracer ^18^F-SynVesT-1, be approximated quantitatively by means of a simplified reference tissue model in HV and is it quantitatively comparable to ^11^C-UCB-J?(ii)Are there regional differences between SV2A PET and ^18^F-FDG PET and do the patterns remain unchanged versus HV?(iii)Can ^18^F-SynVesT-1 PET detect various forms of dementia as accurately as ^18^F-FDG PET?(iv)Does a combination of ^18^F-SynVesT-1 PET with MR-based markers of structural abnormalities and arterial spin labeling allow a better discrimination of different forms of dementia?

Based on literature and current knowledge, the following hypotheses are formulated:

(i)Healthy aging does not result in reduced synaptic density in adults up to 85 years. ^18^F-SynVesT-1 may show a better signal-to-noise ratio and at least equivalent utility for clinical applicability compared to ^11^C-UCB-J.(ii)Simplified quantification of ^18^F-SynVesT-1 PET is possible with white matter (centrum semiovale) as reference region [30, 53] or cerebellum as pseudo-reference region [42].(iii)Synaptic density and arterial spin labeling, as indirect marker of neuronal activity, are related in absolute terms in healthy agers, while regional differences are present that may affect the sensitivity of detection of pathological consequences.(iv)^18^F-SynVesT-1 PET allows accurate detection of patients with an underlying pattern specific for Alzheimer’s disease, frontotemporal dementia and Lewy Body disease, and can discriminate these neurodegenerative diseases from healthy aging and patients with cognitive impairment due to late-life psychiatric disorder.(v)^18^F-SynVesT-1 PET has non-inferior sensitivity and specificity of diagnosis in comparison to ^18^F-FDG PET.(vi)Non-invasive determination of absolute ^18^F-FDG glucose metabolism, ASL and SV2A (SUVR) allows discrimination of patients with late-life psychiatric disorder and neurocognitive disorders with highest accuracy for synaptic density imaging.(vii)Synaptic density PET is better correlated to memory and executive neurocognitive tests compared to ^18^F-FDG PET or ASL, especially in the frontal and medial temporal cortex.

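### The reference diagnosis includes the FDG PET result but does not list SynVesT-1, so the accuracy comparison leans towards FDG by an unknown amount, and anonymized reads do not correct this

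*Protocol article*

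**What the plan says.** The abstract sets the main endpoint: "The main endpoint of the study will be the comparison of the diagnostic accuracy between ^18^F-SynVesT-1 and ^18^F-FDG PET". Hypothesis (v) under Study hypotheses is that SynVesT-1 is non-inferior to FDG in sensitivity and specificity.

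Data analysis and statistics describes the scoring: "data will be compared in terms of accuracy based on the consensus clinical diagnosis (about 6 months after ^18^F-FDG scanning"). The same paragraph lists what that diagnosis rests on: "Consensus clinical diagnosis is based on initial clinical findings and evolution, CSF biomarkers (/ amyloid PET), sMRI and ^18^F-FDG PET results". SynVesT-1 is not in the list.

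The Discussion recognizes the consequence: "the ^18^F-FDG PET result will likely influence the final clinical diagnosis and might result in a bias in favor of ^18^F-FDG PET". Its response is that "anonymized reads will be done also by expert nuclear medicine physicians not involved in the clinical workup".

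Readers are described in two ways within Data analysis and statistics. The three-step evaluation names three nuclear medicine physicians; the statistics paragraph says "scans will be visually assessed by different specialists in nuclear medicine/neurologists".

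**The concern.** When one of two competing tests helps to form the truth against which both are graded, it is credited for agreeing with itself. A SynVesT-1 read that is right, but contradicts a label that FDG decided wrongly, counts as an error. The FDG read in the same patient counts as correct.

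FDG may carry real weight here. Under Study participants, patients are referred for FDG because clinical work-up, neuropsychology, biomarkers and structural MRI left the diagnosis uncertain.

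Anonymizing the scans and using uninvolved readers keeps the study read from being contaminated by the clinical file. It does nothing to the other side of the comparison, the consensus label. At stake is whether an observed deficit of SynVesT-1 could be interpreted at all.

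**Working it through.** **The plan's own figures.** The article gives no figure for this bias. The only non-inferiority figures are under Sample size: margin 10%, α 0.025, power 80%, test-retest variability 5–10%, giving 8, 10 and 12 for true differences of 0, 1% and 2%. With (1.960 + 0.842)² = 7.849 and an assumed SD of 7, the two-group formula 2 × 7.849 × 7² / (10 − d)² gives 7.69, 9.50 and 12.02. A paired form with SD 10 gives 7.85, 9.69 and 12.26. The stated sizes are thus reproduced, to rounding, by a calculation on a continuous measure with test-retest variability as its SD. The 10% is not stated as accuracy points.

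**Model for the bias.** Let:
- w = share of patients in whom the consensus adopts the clinical FDG read (not in the document; 0.1 to 0.3 assumed);
- a = true accuracy of each tracer, equal for both (assumed 0.80 or 0.85);
- k = agreement of the study FDG read with the clinical FDG read;
- g = agreement of the SynVesT-1 read with the clinical FDG read.

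In the other 1 − w of patients the reference errs independently of both scans, so equal accuracy gives no gap. Hence

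spurious gap (FDG minus SynVesT-1) = w × (k − g).

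With four diagnostic classes (AD, FTD, DLB, psychiatric), wrong reads spread evenly over the other three and error correlation φ:

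P(both wrong) = (1 − a)² + φ·a(1 − a)
P(both right) = 1 − 2(1 − a) + P(both wrong)
g = P(both right) + P(both wrong)/3

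**Upper case: independent errors, identical FDG reads (φ = 0, k = 1).**
- a = 0.80: g = 0.64 + 0.04/3 = 0.653; k − g = 0.347.
- a = 0.85: g = 0.7225 + 0.0225/3 = 0.730; k − g = 0.270.

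**Milder case: φ = 0.3, k = 0.93.**
- a = 0.80: g = 0.688 + 0.088/3 = 0.717; k − g = 0.213.
- a = 0.85: g = 0.761 + 0.061/3 = 0.781; k − g = 0.149.

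| Spurious gap, points | w = 0.1 | w = 0.2 | w = 0.3 |
|---|---|---|---|
| Independent, identical reads, a = 0.80 | 3.5 | 6.9 | 10.4 |
| Independent, identical reads, a = 0.85 | 2.7 | 5.4 | 8.1 |
| φ = 0.3, k = 0.93, a = 0.80 | 2.1 | 4.3 | 6.4 |
| φ = 0.3, k = 0.93, a = 0.85 | 1.5 | 3.0 | 4.5 |

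Simulation with subgroups of 50/20/20/20 agrees with these values to within 0.1 point. With w = 0 the expected gap is zero.

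**Consequence for a non-inferiority reading, as illustration only.** Assume n = 110, a 10-point accuracy margin, both tracers 85% accurate, two classes (neurodegenerative or not, for example), identical FDG reads and a 90%-accurate reference where FDG does not decide. The simulated chance of showing non-inferiority is:
- independent errors: 56% at w = 0, 18% at w = 0.2, 3% at w = 0.4;
- error correlation 0.4: 76%, 48% and 20%.

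**The case against.** Four points on the other side carry weight.

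- **The bias is disclosed.** The Discussion names it, gives its direction and explains that FDG is clinically needed. That stands. The finding is that the stated response does not reach the cause, not that the problem was hidden.
- **It works against the new tracer.** A non-inferior result obtained despite it would be conservative. That stands too, and it limits the harm to false failure and to an inflated absolute accuracy for FDG.
- **Independent reads do some good.** The study FDG read is a fresh consensus of three readers and need not match the clinical report, and the tracers' errors are probably correlated because the same readers see the same patients. Both shrink the gap, as the milder case shows, but neither removes it.
- **An FDG-free reference has its own fault.** These patients were uncertain without FDG. Random reference error pulls the tracers together: with true accuracies of 85% and 73% and four classes, the visible gap is 12 × [r − (1 − r)/3], which is 8.8 points for a reference accuracy r = 0.80 and 7.2 for r = 0.70. A truly inferior tracer could look acceptable. This is a good reason not to replace the primary reference.

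A reader might infer that the bias consumes the whole 10% margin and that the trial would then reject SynVesT-1. The document does not support this. The margin is given alongside test-retest variability and not as accuracy points, the statistics paragraph speaks of exploring diagnostic performance and sets no rejection rule, and a 10-point gap at w of about 0.3 needs the least favorable assumptions.

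A reader might also infer that the neurologist readers belong to the team making the diagnosis. The text does not say so; it shows only two reader descriptions that do not match.

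**Conclusion.** The concern holds: the main comparison carries incorporation bias in favor of FDG, and the remedy offered does not remove it. The direction requires only that study FDG reads agree with the clinical FDG result more often than SynVesT-1 reads do, which is to be expected since they read the same scan.

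The size is unknown. For equal true accuracy of 80–85% and FDG deciding 10–30% of labels, it is about 1.5 to 6 points under correlated errors and imperfectly matching FDG reads, and about 3 to 10 points under independent errors and identical reads. The deciding share, the error correlation and the read agreement are all assumptions. A SynVesT-1 success would survive this bias; a SynVesT-1 shortfall could not be interpreted as it stands. No stated figure in the article is wrong on this account.

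**What to change.** Keep the FDG-inclusive consensus as the reference. Before accuracy is scored, prespecify an FDG-independent sensitivity analysis of the same comparison:

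1. AD versus non-AD against CSF or amyloid PET status, in patients who have it.
2. Where feasible, all classes against a six-month diagnosis recorded from clinical course, neuropsychology, CSF/amyloid and structural MRI, with both PET results withheld. The adjudicators should be clinicians who have not seen the FDG result. The neuropsychology should be the routine battery, because the article allows added tests to be chosen partly on FDG.

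State in the plan that a SynVesT-1 shortfall seen only against the FDG-inclusive reference will not be interpreted as inferiority.

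The cost is one additional adjudication of existing files, by people outside the treating team. No new scans are needed and care does not change. The drawbacks should be stated: the FDG-free label is less certain and draws the two apparent accuracies together, and CSF/amyloid status is obtained on suspicion of AD, so it will be missing in some patients and not at random.

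Separately, reconcile the two reader descriptions in Data analysis and statistics (three nuclear medicine physicians, or nuclear medicine specialists and neurologists).
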